# Stop of proton-pump inhibitor treatment in patients with liver cirrhosis (STOPPIT): study protocol for a prospective, multicentre, controlled, randomized, double-blind trial

**DOI:** 10.1186/s13063-022-06232-w

**Published:** 2022-04-12

**Keywords:** PPI, Pantoprazole, Esomeprazole, Side-effects, Complications, Liver cirrhosis, Infections, Hepatic encephalopathy, Mortality, Hospitalization

## Abstract

**Background:**

Proton-pump inhibitors (PPI) are liberally prescribed in patients with liver cirrhosis. Observational studies link PPI therapy in cirrhotic patients with an increased risk for infectious complications, hepatic encephalopathy and an increased risk for hospitalization and mortality. However, patients with liver cirrhosis are also considered to be at risk for peptic ulcer bleeding. The STOPPIT trial evaluates if discontinuation of a pre-existing PPI treatment delays a composite endpoint of re-hospitalization and/or death in patients (recently) hospitalized with liver cirrhosis compared to patients on continued PPI medication.

**Methods:**

The STOPPIT-trial is a prospective, multicentre, randomized, double-blinded, placebo-controlled, parallel-group trial. In total, 476 patients with complicated liver cirrhosis who already receive long-term PPI therapy without evidence-based indication are 1:1 randomized to receive either esomeprazole 20 mg (control group) or placebo (intervention group) for 360 days. Patients with an indication for PPI therapy (such as a recent diagnosis of peptic ulcers, severe reflux esophagitis, severe hemorrhagic gastritis, recent endoscopic therapy for oesophageal varices) are excluded. The primary composite endpoint is the time-to re-hospitalization and/or death. Secondary endpoints include rates of re-hospitalization, mortality, occurrence of infections, hepatic decompensation and acute-on-chronic liver failure. The safety endpoint is defined as manifestation of an evidence-based indication for PPI re-therapy. The impact of PPI continuation or discontinuation on the intestinal microbiota will be studied. The recruitment will take place at 18 study sites throughout Germany. Recruitment has started in April 2021.

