**Fig. 1 Fig1:**
[figure not shown]
Flow chart of the STOPPIT trial. Please note, only key inclusion and exclusion criteria are depicted into this flow chart. Full in- and exclusion criteria are to be found in Table 1

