### Eligibility criteria {10}

Hospitalized, or recently hospitalized, patients with liver cirrhosis with a pre-existing long-term PPI therapy will be screened. Patients with an evidence-based indication for PPI therapy, for example, recent diagnosis of severe reflux esophagitis (LA grade C or D) or peptic ulcers are excluded (for details see Table 1).

**Table 1 Tab1:** In- and exclusion criteria. Patients can be included in the trial, if they fulfil all the inclusion and none of the exclusion criteria

Inclusion criteria	Exclusion criteria
Male and female patients, at least 18 years old.	Diagnosis of reflux esophagitis LA grade C or D by EGD < 2 months prior to the screening visit without PPI therapy for at least 8 weeks prior to the screening visit.
Patients with liver cirrhosis. The diagnosis of liver cirrhosis may be based on (i) histology or (ii) a combination of clinical, laboratory and radiological criteria.	Peptic ulcers diagnosed by EGD < 28 days prior to the screening visit.
Hospitalization or recent hospitalization (0 to 42 days prior to the baseline visit) with complications of liver cirrhosis.	History of endoscopic therapy for oesophageal varices < 14 days prior to the screening visit.
Treatment with PPI for at least 28 days prior to screening.	Life-expectancy < 1 year (at the discretion of the investigator) due to extrahepatic malignancies, metastasized HCC, or other severe extrahepatic diseases (HCC without extrahepatic metastases or reduced life-expectancy < 1 year due to cirrhosis are not regarded as exclusion criteria).
Treatment with a PPI single standard dose/day or less for at least 7 days prior to screening.	Regular intake of NSAID on a daily basis (except for ASA 100 mg/day orally)
Females/males who agree to comply with the applicable contraceptive requirements.	One or more of the following measurements at the time of screening or documented up to 48 h before: ● Temperature > 38.5 °C ● Systolic blood pressure < 90 mmHg and heart rate > 100 bpm ● Catecholamine treatment > 0.1 μg/kg/min (terlipressin is allowed) ● Respiratory rate ≥ 22/min
Non-pregnant, non-lactating females.	Hypersensitivity or intolerance to esomeprazole, substituted benzimidazoles or other excipients of the IMP.
Ability to understand the patient information and to personally sign and date the informed consent to participate in the study, before completing any study-related procedures.	Ongoing therapy with nelfinavir.

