### Criteria for discontinuation or modifying allocated interventions {11b}

Patients who reach the safety endpoint (“evidence-based indication for re-therapy with PPI”; Table 2) will discontinue study medication. However, in case of clinically suspected peptic ulcer disease or signs of upper gastrointestinal haemorrhage rescue PPI treatment is permitted for up to 72 h or until an oesophago-gastro-duodenoscopy (EGD) is performed. If the EGD does not reveal a safety endpoint, rescue PPI therapy will be stopped and the patient continues study medication.

**Table 2 Tab2:** Primary, secondary and safety endpoints of the trial

Primary composite endpoint	Secondary endpoint
1.) Unplanned re-hospitalization	1.) Death
2.) Death	2.) Unplanned re-hospitalization
	3.) Any infection and differentiated by site of infection (SBP, pneumonia, urinary tract infection, blood stream infection, Clostridium difficile-associated enterocolitis, Norovirus infection, SARS-CoV-2 infection, others)
	4.) Acute hepatic decompensation and ACLF
	5.) Upper or lower gastrointestinal bleeding event
	**Safety endpoint:** Evidence based re-therapy with PPI due to the occurrence of any the following conditions:
	1.) Peptic ulcer diagnosed by EGD
	2.) Reflux esophagitis LA grade C or D diagnosed by EGD
	3.) Severe hemorrhagic gastritis diagnosed by EGD and histology
	4.) Mallory-Weiss syndrome diagnosed by EGD

*SBP* spontaneous bacterial peritonitis, *SARS-CoV-2* severe acute respiratory syndrome coronavirus 2, *ACLF* acute-on-chronic liver failure, *PPI* proton-pump inhibitors, *EGD* oesophago-gastro-duodenoscopy

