### Participant timeline {13}

Recruitment is planned to be completed within three years. With a trial duration 360 days per patient, time of first-patient-in to last-patient-out is four years. Figure 1 provides an overview of the trial design. After completion of the informed consent process, the screening visit will take place. Randomization will take place 0 to 14 days after screening during the baseline visit (visit 1, day 0). The study is split into two parts: “dose tapering phase” (days 1–14; tapering of the PPI dose in a blinded fashion, see above) and “main study phase” (days 15–360). Study visits and telephone interviews take place at the time-points indicated in Table 3. Study procedures during the respective visits and telephone interviews are summarized in Table 4.

**Table 3 Tab3:** Visits and time points

Screening visit	Up to 14 days before baseline
**Visit 1 (baseline)**	Day 0
**Visit 2**	Day 28 (± 2 days)
**Visit 3, 4, 5, 6**	Day 90, 180, 270, 360 (± 7 days, respectively)
**Telephone interview 1**	Day 14 (± 2 days)
**Telephone interview 2, 3**	Day 135, 225 (± 7 days, respectively)

**Table 4 Tab4:** Study procedures

Procedure	Screening	Baseline visit	Visits 2–6	Telephone interviews
Informed consent	X			
In-/exclusion criteria	X			
Randomization		X		
Medical history/demographics	X	X		
Adverse events/concomitant medication/endpoint assessment		X	X	X
Physical examination/height and weight		X	X	
Vital sign assessment	X	X	X	
Laboratory (haematology, biochemistry)		X	X	
Pregnancy test	X			
Stool samples & biobanking		X	X (visit 3)	
Ultrasound		X	X (visit 4, 6)	
Distribution and/or return of study medication and patients diaries		X	X	

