Importantly, sudden PPI withdrawal in the intervention group may lead to clinically relevant overproduction of gastric acid with a recurrence of dyspeptic symptoms [53–55], which could lead to an increased risk for protocol violations (like the intake of PPIs or other acid-suppressive drugs). Therefore, PPI discontinuation will be achieved after dose tapering as previous data suggest a clinical benefit of dose tapering instead of abrupt withdrawal of PPI therapy [55].

In- and exclusion criteria are designed to ensure that the study population represents all patients with complicated liver cirrhosis in whom PPI discontinuation is feasible and may have positive effects on patients’ outcome: Especially hospitalized patients with complications of liver cirrhosis are at risk for re-hospitalization [20, 30, 56] and hospitalization itself is associated with increased mortality in this population [50]. Furthermore, the incidence of an infection (which is regarded a complication of cirrhosis in our protocol) is often a deteriorating event in the course of cirrhotic disease leading to ACLF [57]. As the study aims to evaluate the discontinuation of widely practiced “prophylactic” long-term PPI prescription without strong indication, a PPI therapy has to be documented for ≥ 28 days prior to screening. However, only patients taking a single PPI standard dose per day or less for at least 7 days are included in the trial, as patients receiving higher doses of PPI might be at an increased risk to suffer from gastric acid rebound symptoms [53–55] despite our PPI dose tapering protocol.

The exclusion criteria represent evidence-based indications for PPI therapy also in cirrhosis patients according to the German guidelines [58–60]. In these patients, discontinuation of PPI therapy might be harmful. Patients who underwent endoscopic therapy for oesophageal varices < 14 days prior to screening are also excluded, as PPI therapy may reduce the size of banding-ulcers after variceal band ligation [45, 46]. Patients with a life-expectancy below 1 year due to extrahepatic diseases or malignancies are excluded to avoid confounding of the primary efficacy endpoint, as these patients have a high risk to reach the primary endpoint independently from cirrhosis or the trial intervention. Also, patients who are regarded clinically unstable are excluded from the trial.

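### The abstract excludes severe haemorrhagic gastritis but the full criteria list in Table 1 does not, and the Table 1 windows leave uncovered any PPI indication found between screening and randomisation

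*Protocol article*

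**What the plan says.** The abstract (Methods) gives examples of PPI indications that bar entry and names gastritis among them: "severe hemorrhagic gastritis, recent endoscopic therapy for oesophageal varices) are excluded". The Eligibility criteria section states the principle of exclusion more generally, in a sentence that begins "Patients with an evidence-based indication for PPI therapy, for example, recent diagnosis of severe reflux esophagitis (LA grade C or D) or peptic ulcers are", and sends the reader to Table 1 for details.

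Table 1 is the operative list. The Figure 1 legend says "Full in- and exclusion criteria are to be found in Table 1", and the Table 1 caption sets the rule: "Patients can be included in the trial, if they fulfil all the inclusion and none of the exclusion criteria". Its endoscopic exclusions are tied to screening, for example "Peptic ulcers diagnosed by EGD < 28 days prior to the screening visit". Reflux oesophagitis (LA grade C or D) and endoscopic variceal therapy have windows with the same anchor.

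Table 2 defines the safety endpoint as evidence-based PPI re-therapy for any of four conditions. The third is "Severe hemorrhagic gastritis diagnosed by EGD and histology" and the fourth is Mallory-Weiss syndrome. Section 11b says that patients who reach this endpoint discontinue study medication.

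On timing, the Participant timeline says "Randomization will take place 0 to 14 days after screening during the baseline visit (visit 1, day 0". Table 4 marks in-/exclusion criteria in the screening column only. The Discussion describes the purpose of the list: "The exclusion criteria represent evidence-based indications for PPI therapy also in cirrhosis patients".

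**The concern.** The trial withdraws PPI, under blinding, from patients who are meant to have no evidence-based reason to take it. The entry list therefore defines the population and is also the first protection for patients allocated to placebo. Two features of the text weaken it. One condition is excluded in the abstract and ends study medication under Table 2, but has no line in Table 1. And an indication diagnosed after screening but before day 0 falls outside every dated window.

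In either case, sites working from Table 1 could randomise a patient whom the abstract or the general eligibility sentence describes as excluded, and 1:1 allocation would send about half of such patients to placebo. With 18 sites, some may follow Table 1 literally and others the general sentence, so the population would depend on local reading.

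**Working it through.** No figure in the plan enters this point. The check is a comparison of lists and of time anchors.

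**Step 1: the lists.**

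| Condition | Abstract, Methods | Table 1 (entry) | Table 2 (ends study medication) |
|---|---|---|---|
| Peptic ulcer | excluded | yes, dated window | yes |
| Severe reflux oesophagitis (LA C or D) | excluded | yes, dated window with a qualifier on prior PPI therapy | yes |
| Severe haemorrhagic gastritis | excluded | **absent** | yes |
| Mallory-Weiss syndrome | not named | absent | yes |
| Recent endoscopic variceal therapy | excluded | yes, dated window | not listed |

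Table 1 carries three of the four conditions that the abstract names, and two of the four that Table 2 names. Severe haemorrhagic gastritis is the only row where the abstract and Table 2 both treat the condition as a PPI indication and Table 1 is silent.

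**Step 2: does anything else in Table 1 catch gastritis?** No criterion covers other PPI indications, and no inclusion criterion requires that an indication be absent. The limit to a single standard PPI dose for at least 7 days before screening may keep out some such patients, but it turns on dose and not on diagnosis. Under the caption's rule, a patient with gastritis who meets the other criteria is eligible.

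**Step 3: the time anchors.** Ulcer: less than 28 days before screening. Oesophagitis: less than 2 months before screening. Variceal therapy: less than 14 days before screening. Randomisation: 0 to 14 days after screening. Suppose screening is on day −14 and an endoscopy on day −9 shows an ulcer. The diagnosis falls 14 − 9 = 5 days after screening, so it is not prior to screening at all and the criterion is not met. The same holds for the other two windows. The uncovered interval is between 0 and 14 days, depending on when the baseline visit takes place.

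**Step 4: is eligibility looked at again before randomisation?** In part. The hospitalisation criterion runs to the baseline visit, and the serum pregnancy test is tied to first treatment. At baseline Table 4 also lists medical history and the combined row for adverse events, concomitant medication and endpoints. None of these is described as a check for a PPI indication, and finding one there would still not trigger a screening-anchored criterion.

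**The case against.** The strongest reply is that the general eligibility sentence already excludes anyone with an evidence-based indication, has no screening anchor and gives its conditions only as examples. That shows the intent, and it is why this is an inconsistency and not a deliberate choice. It does not settle the matter, because the sentence defers to Table 1 for details and Table 1 is presented as complete.

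A second reply is that an article condenses the full protocol, here version 2.0, which may contain a gastritis criterion or a day-0 confirmation. That is possible. But the point does not rest on missing detail: two statements in the article conflict, and they need correcting even if the full protocol is sound.

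Some stronger readings are tempting and are not supported:

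- *All criteria are checked only at screening.* The hospitalisation and pregnancy criteria run past it. The gap concerns the PPI-indication criteria.
- *Mallory-Weiss syndrome must be an entry exclusion because Table 2 lists it.* The abstract does not name it, and nothing in the document requires the entry list to mirror the on-trial list.
- *Affected patients already meet the safety endpoint on day 0 and distort the safety comparison.* Table 2 speaks of the occurrence of a condition, and it is unclear whether a diagnosis known before day 0 would count. Randomisation would be expected to spread such patients evenly, so no directional bias is shown.
- *A percentage of spurious safety events can be given.* The document reports neither how common these conditions are at entry nor an expected safety-event rate.

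**Conclusion.** The point holds as an internal inconsistency with a consequence for patient safety and for the definition of the population. The gastritis mismatch is certain from the text. The timing gap is narrower: it lasts at most 14 days, may be zero for a given patient, and matters only if an endoscopy in that interval reveals an indication. That is plausible in patients who are in hospital or recently discharged with complications of cirrhosis.

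The number affected among the 476 planned patients cannot be derived, and no effect on power or on the primary hazard ratio is claimed. The conclusion assumes that sites apply Table 1 as written. If the full protocol already resolves both matters, what remains is a correction to the article. It should be fixed, because the remedy is cheap and the safeguard concerns patients allocated to withdrawal.

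**What to change.** 1. Reconcile the abstract, the Eligibility criteria section with Table 1, Table 2 and the Discussion, so that one list states which PPI indications exclude a patient at entry. Whether severe haemorrhagic gastritis and Mallory-Weiss syndrome belong on it is for the clinical leads to decide.
2. In Table 4, mark the in-/exclusion check at the baseline visit as well as at screening, to be completed before randomisation.
3. Reconcile the screening-anchored windows in Table 1 with the randomisation date, so that indications arising between screening and day 0 are covered. Step 2 alone is not enough: a baseline tick box would show a new ulcer, but the current wording would still not exclude the patient.

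The cost is a short amendment, one confirmation field in the baseline eCRF and a few more screening failures. If version 2.0 of the full protocol already contains these rules, only the article's text needs correcting.

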**Discussion:**

The STOPPIT trial is the first clinical trial to study the effects of PPI withdrawal on relevant outcome variables in patients with complicated liver cirrhosis. If the hypothesis that PPI withdrawal improves clinical outcomes of cirrhosis patients is confirmed, this would argue for a strong restriction of the currently liberal prescription practice of PPIs in this population. If, on the other hand, the trial demonstrates an increased risk of gastrointestinal bleeding events in patients after PPI withdrawal, this could create a rationale for a more liberal, prophylactic PPI treatment in patients with liver cirrhosis.

**Trial registration:**

EU clinical trials register EudraCT 2019-005008-16 (registered December 27, 2019). ClinicalTrials.gov NCT04448028 (registered June 25, 2020). German Clinical Trials Register DRKS00021290 (registered March 10, 2021).

## Administrative information

Note: the numbers in curly brackets in this protocol refer to SPIRIT checklist item numbers. The order of the items has been modified to group similar items (see http://www.equator-network.org/reporting-guidelines/spirit-2013-statement-defining-standard-protocol-items-for-clinical-trials/).

## Introduction

### Background and rationale {6a}

Proton-pump inhibitors (PPI) are liberally and widely prescribed in patients with liver cirrhosis without a clear evidence-based indication [1–9]. Observational and retrospective studies suggest that PPI use in cirrhosis patients may be a risk factor for infections [10–14], especially spontaneous bacterial peritonitis (SBP) [8–10, 15, 16]. Increased SBP rates in cirrhotic patients may be explained through PPI-associated microbiotic shifts leading to small intestinal bacterial overgrowth and bacterial translocation [17–20]. PPI therapy was also suggested as a possible risk factor for pneumonia [10, 21, 22] and *Clostridium difficile* infections in cirrhotic patients [23]. However, other observational studies found no evidence for an association of PPI use and the risk of development of pneumonia [24], SBP [25–27] or infections in general [27]. Moreover, an association between episodes of (overt) hepatic encephalopathy and PPI use has been reported [6, 7, 9, 28, 29]. Infections and hepatic encephalopathy may often cause hospitalizations of cirrhotic patients. PPI use at discharge and PPI-mediated microbiotic shifts have also been associated to early re-hospitalization [20, 30, 31]. Also, PPI use has been reported to be an independent predictor for mortality in cirrhotic patients [5, 6, 10, 32, 33] and in a large North-American veteran cohort, as well as in patients with malignant diseases [34–36]. Again, other studies found no association between PPI use and mortality of cirrhotic patients [4, 27].

Thus, current evidence, even if not unambiguous, suggests an unfavourable risk profile of PPI in patients with liver cirrhosis. However, this patient population is considered to be at a high risk of gastrointestinal haemorrhage from peptic ulcers [37–40]. Importantly, peptic ulcer bleeding in patients with liver cirrhosis is associated with an increased mortality as compared to patients without cirrhosis [41–43], and mortality rates of cirrhotic patients with peptic ulcer bleeding are comparable to cirrhotic patients with bleeding from oesophageal varices [44]. Therefore, generous PPI use may also have a yet unproven preventive effect against upper gastrointestinal bleeding events. Short term use of PPIs for up to 10 days may reduce ulcer size after endoscopic variceal band ligation [45, 46], but there is no evidence for protective effects of PPI therapy against portal hypertension-related bleeding in cirrhotic patients who did not receive endoscopic ligation therapy [47].

### Objectives {7}

The primary objective of the trial is to determine the time to first unplanned re-hospitalization or death (composite endpoint) in patients with liver cirrhosis who discontinue long-term PPI therapy (intervention group) as compared to patients who continue PPI therapy (control group) over a period of 12 months (360 days). Secondary objectives include an assessment and comparison of the following endpoints in the two groups:
Time to death and mortality (overall and liver-related),Time to and rate of unplanned re-hospitalization,Overall infection rates and infections rates differentiated by the site of infection,Rate of acute hepatic decompensation and acute-on-chronic liver failure (ACLF),Rate and source of upper and lower gastrointestinal bleeding events.

Furthermore, the changes in the intestinal microbiota in both groups and their impact on the primary endpoint will be assessed. The potential pharmacoeconomic impact of PPI discontinuation in patients with liver cirrhosis will be studied, too.

